### Statistical analysis

The primary outcome, the number of days alive and free of ventilation at day 28, will be analyzed using Cox’s regression. Possible imbalance between groups will be modeled in the Cox model. *P*-values of 0.05 are used for statistical significance. When appropriate, statistical uncertainty will be expressed by the 95 % confidence levels. All statistical analyses will be performed with the R language and environment for statistical computing.

Continuous normally distributed variables will be expressed by their mean and standard deviation or when not normally distributed as medians and their interquartile ranges. Categorical variables will be expressed as n (%). To test groups Student’s *t*-test will be used, if continuous data is not normally distributed the Mann-Whitney *U*-test will be used. Categorical variables will be compared with the Chi-square test or Fisher’s exact tests. Time dependent data will be analyzed using a proportional hazard model adjusted for possible imbalances of patients’ baseline characteristics. Analysis will be performed with R statistics version 3.0.2 (R Foundation, Vienna, Austria). Patient characteristics will be compared and described by appropriate statistics.

The goal of the primary analysis is to quantify the effect of ventilation using low tidal volumes versus ventilation using high tidal volumes on the number of ventilator-free days and alive at day 28. Statistical analysis will be based on the intention-to-treat principle. We will also perform a per-protocol analysis, comparing patients who received lower tidal volumes and patients who received higher tidal volumes. Other secondary analyses include*:* patients who had pneumonia versus patients without pneumonia, and patients with sepsis versus patients without sepsis.

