### Randomization and blinding

Randomization will be performed using a dedicated, password protected, SSL-encrypted website with ALEA® software (TenALEA consortium, Amsterdam, The Netherlands) using random block sizes and is stratified only per ICU and per intubation location (that is intubated in the ICU or before ICU admittance in the emergency room or operation room). When, after randomization, consent is rejected, the patient is excluded. Due to the nature of the intervention, blinding is not possible.

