### Follow-up

On ICU admission and within the first 24 hours, demographic and baseline data, as well as data on disease severity are collected. Data collection includes: gender, age, height, weight, reason for ICU admission, reason for ventilation, cause of respiratory failure, the Acute Physiology and Chronic Health Evaluation II (APACHE II) score and the Simplified Acute Physiology Score II (SAPS II).

Data on standard of care and clinical outcome variables (described below) are collected on a daily basis every day until day 28, discharge of the ICU or death, whichever comes first. Data on duration of ventilation, length of stay in ICU and hospital, location of the patient (in ICU, hospital, other facility, or home) and life status (alive or deceased) are assessed on days 28 and 90.

The following variables are collected daily: respiratory status; intubation status (if extubated: time of extubation/if re-intubated: time of re-intubations) tracheostomy status (if tracheostomized: time of tracheotomy), invasiveness of ventilation (invasive, non-invasive, or intermittent ventilation via tracheostomy), need for decreasing instrumental dead space; development of pulmonary complications (moderate or severe ARDS, pneumonia, atelectasis and pneumothorax); cumulative use and duration of sedatives and neuromuscular blocking agents; sedation score using the RASS [27, 28]; level of pain (NRS or VAS or CCPOT or BPS); delirium score with the Confusion Assessment Method for ICU (CAM-ICU) score [30, 31]; presence of ICU-acquired weakness using Medical Research Council (MRC) score [32] or Grip Strength Assessment [33].

The following mechanical ventilation parameters are collected within 1 hour before and 1 hour after randomization, and every day at a fixed time point until cessation of ventilation: tidal volume in ml and ml/kg PBW, respiratory rate, level of PEEP, peak and plateau pressures, or level of pressure support and maximal airway pressure, inspiration to expiration ratio, inspired oxygen fraction, minute volume, pulmonary compliance, Lung Injury Score (LIS: based on chest X-ray findings, PaO_2_/FiO_2_, PEEP level and respiratory compliance) [34] and Oxygenation Index [35].

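### Covariates for the primary Cox model are chosen by imbalance rather than fixed in advance; the rule does not provide for the stratification factors and admits severity scores recorded after treatment has begun

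*Protocol article*

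**What the plan says.** The Statistical analysis section assigns the primary outcome to Cox regression and adds: "Possible imbalance between groups will be modeled in the Cox model". For time-dependent data it repeats the idea, "proportional hazard model adjusted for possible imbalances", there referring to baseline characteristics. It also says: "Patient characteristics will be compared and described by appropriate statistics". It gives neither a covariate list nor a criterion for imbalance.

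Under Randomization and blinding, allocation uses random block sizes and "is stratified only per ICU and per intubation location". The analysis section mentions neither factor.

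Under Follow-up: "On ICU admission and within the first 24 hours, demographic and baseline data, as well as data on disease severity are collected". Nine items are listed: gender, age, height, weight, reason for ICU admission, reason for ventilation, cause of respiratory failure, APACHE II and SAPS II.

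Under Statistical considerations, randomisation and the assigned ventilation are to begin within 1 hour of the start of ventilation, or within 1 hour of admission if ventilation began in the emergency or operation room.

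**The concern.** A rule that adds covariates according to imbalance makes the primary model a function of the data. Two analysts following the sentence could fit different models, and neither would be the prespecified one. Chance imbalance is also a poor guide to what belongs in a model: prognostic strength matters, and it can be named beforehand.

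The rule fits this design badly in two ways. It tends to pass over the factors that the randomisation balances, which the analysis would normally reflect. It also leaves room for variables labelled baseline whose collection window runs past the start of treatment. A difference between arms in such a variable may be an effect of treatment, and adjusting for it means that the model no longer estimates the total effect of the assigned strategy.

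**Working it through.** **1. The plan's own figure, for scale.** Inputs from Statistical considerations: difference 1 day, SD 5, two-sided 0.05, power 80%. n = 2(1.96 + 0.8416)² × 5² / 1² ≈ 393 per arm (394 with the exact t distribution). The stated 397 is close and gives 80.4% power; 397 × 1.2 = 476.4, the stated 476. This is a t-test calculation, so steps 2 to 4 use the same linear approximation. The variance shares (R²) and score shifts are assumptions, not document figures.

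**2. Strata not in the model.** There are 5 ICUs × 2 intubation locations = 10 strata. With balanced strata explaining a share R² of variance:
- True size of the nominal 5% test = 2[1 − Φ(1.96/√(1 − R²))]: 4.4% at R² = 5%, 3.9% at R² = 10%.
- Power: the reported SE is 5√(2/397) = 0.3549, so the critical difference is 1.96 × 0.3549 = 0.6956. The true SE is 0.3549√(1 − R²).
- R² = 5%: true SE 0.3459. Omitted, Φ((1 − 0.6956)/0.3459) = 81.1%; included, Φ(1/0.3459 − 1.96) = 82.4%.
- R² = 10%: true SE 0.3367. Omitted, Φ(0.904) = 81.7%; included, Φ(1.010) = 84.4%.

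A simulation at R² = 10% agrees: size 4.1% omitted and 5.2% included (3,000 runs; Monte Carlo SE √(0.05 × 0.95/3000) ≈ 0.4 points), and power 80.5% and 83.8% (2,000 runs).

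**3. Covariates picked by imbalance.** The article sets no threshold, so take p < 0.05 as an illustration. If k independent characteristics are compared, the chance that at least one is flagged by luck is 1 − 0.95^k: 23% for k = 5 and 37% for k = 9. The nine listed items are correlated, so 37% only illustrates how easily the model changes. It is not an error rate.

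Simulation with 397 per arm and 8 independent covariates that jointly explain 20% of variance:
- No effect, strata unrelated to outcome: type I error 3.8% with selection at p < 0.05, against 4.2% unadjusted. A fixed selection rule does not inflate the error.
- True effect 1 day, strata explaining 10%: power 80.5% unadjusted, 81.7% with imbalance-selected covariates, 88.5% with all 8 fixed in advance.

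**4. A score recorded after treatment starts.** With a 24-hour window and treatment within 1 hour, up to about 24 − 1 = 23 hours of the window can follow the start of treatment. If treatment shifts the score by s SD and the score explains a share R² of outcome variance, the bias has size 5 × √R² × s days.
- R² = 20%: 0.22, 0.45 and 0.67 day for s = 0.1, 0.2 and 0.3. Simulated values are 0.22, 0.46 and 0.69, with type I error of about 10%, 28% and 57% (1,500 runs each).
- R² = 10%: 0.16, 0.32 and 0.47 day.

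The sign depends on the shift. Higher severity goes with fewer ventilator-free days, so if low tidal volumes raise the score, adjustment overstates their benefit; if they lower it, adjustment understates it.

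**5. Carry-over to Cox regression.** These sizes do not transfer directly. In a Cox model covariates do not act by shrinking a residual variance, and adjustment changes which hazard ratio is estimated.

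**The case against.** The strongest reply is that this is a condensed article, and that covariate lists and the handling of strata commonly sit in an analysis plan that is not shown. That stands as regards silence: the absence of a list alone would be no finding. It does not dispose of the point, because the article states a rule, and it is the rule that makes the model depend on the data.

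Several stronger readings are tempting, and the article does not support them:
- **The model will adjust for APACHE II or SAPS II.** Nothing says so. The rule only leaves them eligible.
- **ICU and intubation location are excluded.** They are not mentioned; exclusion is not stated.
- **Type I error is inflated.** Step 3 shows no inflation under a fixed threshold, and omitting the strata is conservative. An open threshold searched for a favourable result could inflate it, but the Discussion says analyses are performed blinded and nothing suggests such a search.
- **The intervention changes oxygenation and pH by design.** Table 1 sets the same pH and oxygenation targets and the same FiO2-PEEP combinations in both arms. Only respiratory rate is described as typically different. The components of the scores are not given.
- **Adjustment would remove part of the effect.** The direction is not established.
- **The severity window is almost all after randomisation.** It runs from ICU admission, and one stratum is intubated in the ICU. For a patient intubated hours after admission, much of the window may come before randomisation.

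It is also fair that the magnitudes rest on assumed inputs and a linear model.

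**Conclusion.** The point holds in this limited form. The stated rule makes the covariates of the primary model depend on observed imbalance, makes no provision for the two stratification factors and would rarely select them, and does not bar severity scores whose window overlaps treatment.

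The strata part is modest: a somewhat conservative test and about 1 to 3 points of power, if the strata explain 5 to 10% of variance. The severity-score part is conditional but could be larger: about 0.2 to 0.7 day of bias in either direction against a 1-day target, if such a score is used, explains 10 to 20% of variance and is shifted by 0.1 to 0.3 SD. No figure in the article fixes these inputs. The case for the change does not depend on them: a prespecified model is better whatever their values. The stated sample size is unaffected.

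**What to change.** Replace the imbalance sentence with wording such as: the primary Cox model includes, or is stratified by, ICU and intubation location, and includes a short named list of covariates measured before randomisation, whatever the observed balance. The trial team should choose the list; age, reason for admission and a respiratory measurement taken before randomisation are examples. Add that 24-hour severity scores are not adjusted for unless computed from pre-randomisation values only. Apply the same wording to the time-dependent analyses. Baseline characteristics can still be described by arm, but the comparison should not decide what enters the model.

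The cost is small. Age and reason for admission are already recorded, and ventilation variables are collected within 1 hour before randomisation. Small centres may need pooling, or a Cox model stratified by centre. The hazard ratio becomes conditional on the covariates, which the report should state. The article lists the trial as recruiting, so the change can be made before analysis.

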### Study organization

The steering committee is composed of the principal investigator, the coordinating investigator, the local investigators in the participating ICUs, and six (inter)-national experts of ventilation who contribute to the design and revisions of the study protocol. The coordinating investigator is responsible for administrative management and communication with the local investigators and provides assistance to the participating clinical sites in trial management, record keeping and data management. The coordinating investigator helps in setting up local training in the participating ICUs to ensure the study is conducted according to the ICH-GCP guidelines, to guaranty integrity of data collection and to ensure timely completion of the case report forms. The local investigators provide structural and scientific leadership. They guarantee the integrity of data collection and ensure timely completion of the case report forms.

An independent monitor is installed to perform study monitoring. Remote monitoring by means of queries on the database will be done by a statistician and analyzed by the monitor to signalize early aberrant patterns, trends, issues with consistency or credibility and other anomalies. On-site monitoring will comprise controlling presence and completeness of the research dossier and the informed consent forms, source data checks will be performed in the files of 25 % of the patients. Each ICU will be visited at least once every year.

An independent Data and Safety Monitoring Board (DSMB) watches over the ethics of conducting the study in accordance with the *Declaration of Helsinki*, monitors safety parameters and the overall conduct of the study. The DSMB is composed of five independent individuals ([name] [name], [name], [name], [name] and [name]). The DSMB will meet by conference calls. The first meeting is scheduled after the first 150 patients. Subsequent to this meeting the DSMB will meet every 6 months.

As this study compares two treatment strategies that are used in standard care, no related serious adverse events are expected. All unexpected adverse events will be reported to the DSMB. Any report and/or advice of the DSMB will be send to the sponsor of the study, the Academic Medical Center, Amsterdam, The Netherlands. Should the sponsor decide not to fully implement advices of the DSMB, the sponsor will send the advice to the reviewing Institutional Review Board, including a note to substantiate why (part of) the advice of the DSMB will not be followed.

## Discussion

PReVENT is the first randomized controlled trial that is sufficiently powered to test the hypothesis that a ventilation strategy using low tidal volumes, as compared to a ventilation strategy using high tidal volumes, benefits patients without ARDS with regard to the clinically relevant endpoint of duration of ventilation.

It is increasingly becoming clear that ventilation *per se* has the potential to initiate lung injury or ARDS, mainly due to over-distension of (parts of) the lung [2]. Since a generally employable alternative treatment for ventilation is not yet at our disposal, the prevention of over-distension and lung injury should be the target. Earlier clinical studies indicated that ventilation using low tidal volumes could prevent development of lung injury by avoiding excessive stretch, and that high tidal volumes are more likely to cause damage in patients without ARDS [22]. A sufficiently-powered randomized controlled trial investigating the effects of low tidal volume ventilation in patients without ARDS is presently lacking. PReVENT follows an earlier randomized controlled trial in The Netherlands [21] that was prematurely stopped because of an unexpected benefit (that is reduction in development of new ARDS). In contrast to the previous randomized controlled trial, PReVENT uses duration of ventilation as primary endpoint. This endpoint is objective and foremost clinically relevant. Namely, protracted use of ventilation is associated with serious physiological and psychological sequelae. Complications associated with ventilation are well-known and include VAP and ICU-acquired weakness. Psychological sequelae associated with protracted use of ventilation are post-traumatic stress disorder [38–40], anxiety and depression [41], delirium [30, 42] and cognitive deficits [43]. Also, from an economic perspective, any intervention that shortens duration of ventilation and/or ICU length of stay is highly relevant.

We anticipate PReVENT to be a highly feasible trial, as the study procedures are straightforward, without difficult or complex interventions. Furthermore, PReVENT uses a deferred consent strategy to include patients rapidly in the trial, and also those who are admitted during evenings or nights when researchers are frequently not around to ask for informed consent. This will create a study population representative of the average ICU population. A lean study protocol, not involving complex analyses and sampling of, for example, blood or lung lavage fluid, will limit the burden on daily activities.

PReVENT specifically prescribes a range of tidal volumes for each group. We aim to ventilate patients with tidal volumes of 4 ml/kg PBW or 10 ml/kg PBW, depending on randomization, but physicians and nurses are allowed to change the tidal volumes following strict guidelines: in case of a too high respiratory rate (in the lower tidal volume group), the tidal volume size can be increased stepwise to 6 ml/kg PBW - in case of too high airway pressures (in the higher tidal volume group), the tidal volume size can be decreased stepwise to 8 ml/kg PBW. Experiences with the study protocol suggest that the average tidal volumes will be 5 and 9 ml/kg PBW [21]. Notably, we aim for tidal volumes lower than 6 ml/kg PBW in the lower tidal volume group, since previous investigations suggest more benefit from further reductions in tidal volume size in patients with ARDS [10, 44–47]. Certainly, use of lower tidal volumes mandates use of higher respiratory rates to prevail adequate minute ventilation. Higher respiratory rates are typically seen as uncomfortable and maybe even unfeasible in non-sedated non-paralyzed patients. However, neither observational studies [48] nor the abovementioned randomized controlled trial in The Netherlands [21] suggested this to be a realistic problem. This was confirmed in a recently published meta-analysis that showed no differences in sedation needs between strategies using lower tidal volumes and those using higher tidal volumes [37].

At present, the size of tidal volumes in patients without ARDS is highly variable. For instance, two recent meta-analyses show that 11 % of patients are ventilated with tidal volumes of 4 to 6 ml/kg PBW and 53 % of patients are ventilated with tidal volumes > 8 ml/kg PBW [37, 49]*.* Also, the proposed level of PEEP is that level that is used as standard care in the participating hospitals, which is usually 5 cmH_2_O. The study protocol, however, advises on the best FiO_2_-PEEP-combinations [6].

From a physiological viewpoint one may argue that the seemingly ‘one size fits all’ approach that is used in this study does not allow individual titrations of tidal volumes. Indeed, more sophisticated approximations of the functional lung volume are possible: for example, by driving pressures as recently reported to be possibly more efficient in patients with ARDS [50]. It is highly uncertain, though, whether a similar relationship between driving pressure and outcome exists in patients without ARDS. Notably, the study protocol of PReVENT allows individual titrations, as tidal volume size could be adjusted depending on respiratory rate and airway pressures.

A patient’s height is necessary for calculating the size of tidal volumes to be used, as PBW is a function of patient’s height. Preferably we use height as reported in the medical record of each individual patient. If absent, for example, in patients who are acutely admitted from outside the hospital or when the medical record is not available, nurses and researchers must use tape measures. Nevertheless, measuring height in supine patients with a tape measure could result in height values slightly different from those obtained by measuring height in a standing patient [51]. This bias cannot be avoided.

In PReVENT patients will be provisionally included under a strategy of deferred consent. The reasons to choose for such a strategy are twofold: first, many if not all patients admitted for ventilation are incompetent to give informed consent; second, obtaining informed consent from a legal representative takes on average up to half a day [52]. Both experimental [53] and clinical studies [54–56] clearly show ventilation-induced lung injury is caused within hours. To keep the period of ‘uncontrolled’ ventilation as short as possible, using deferred informed consent, we can randomize patients within 1 hour of start of ventilation, or within 1 hour after arrival in the ICU.

Patients who present with ARDS according to the Berlin definition [25] are excluded from participation in PReVENT. In the first hour after intubation and start of ventilation, usually shortly after admission to the ICU, the medical history could be incomplete and the chest X-ray reading could not yet be available, leaving the attending physician only with the PaO_2_/FiO_2_ to exclude ARDS. Post-intubation atelectasis, usually short-lasting, cardiac failure and fluid overload, however, are the important causes for hypoxia in these patients. As patients with other reasons than ARDS for hypoxia should not be excluded from participation in PReVENT, we decided the following: in case the medical history is incomplete and the chest X-ray is not yet obtained, a PaO_2_/FiO_2_ between 200 and 300 mmHg is not a reason for excluding a patient from participation - patients with a PaO_2_/FiO_2_ < 200 mmHg, however, are not accepted, unless hypoxia is likely explained by cardiac failure or fluid overload. This approach is pragmatic but may not be perfect: it is possible that a small proportion of patients are diagnosed with ARDS in the following hours. Of course, then tidal volumes must be lowered to 6 ml/kg PBW - these patients, however, do not leave the trial, as the primary analysis follows the intention-to-treat principle. It is also possible that patients with a PaO_2_/FiO_2_ < 200 mmHg are excluded while not having ARDS. Here we prefer safety, and accept the risk of bias.

PReVENT knows several strengths. First, the study protocol is pragmatic and easy to follow. The trial is highly feasible, and inclusion of patients is not difficult. Also, PReVENT will be performed in the ICUs of different types of hospitals, increasing the generalizability of its findings. Furthermore, early contamination with the other ventilation strategy is prevented as much as possible by the rule that patients must be randomized to one of the two arms of the study within an hour.

One important limitation of PReVENT is that blinding is not possible due to the nature of the intervention, which could induce bias. However, the weaning process, which directly influences the primary outcome, stays within the hands of the attending ICU physician and nurse with no specific interest in PReVENT, and all analyses are performed in a blinded fashion. Second, sedation practice could mask potential patient discomfort caused by one or both ventilation strategies. However, it is stressed to aim for similar sedation aims in both arms of the trial. Third, when ventilation mode is switched from controlled - to spontaneous ventilation, tidal volumes may become less controllable and out of the predefined ranges. In a previous randomized controlled trial we experienced this to happen only within some hours after the switch; thereafter, tidal volume size was less difficult [21]. As with all multicenter studies, differences in care practice and complications such as ICU-acquired infections amongst the participating centers could be confounding factors. Also, we chose to accept a heterogeneous group of patients alike in a preceding trial of critically ill patients testing a similar intervention, and not to stratify for certain conditions [21]. If subgroups are large enough, we could decide to perform a *post-hoc* analysis.

In conclusion, PReVENT is the first national, investigator-initiated randomized controlled trial that is adequately powered to test the hypothesis that a ventilation strategy using low tidal volumes of 6 down to 4 ml/kg PBW benefits ICU patients without ARDS at onset of ventilation.

